### Intervention fidelity

Health visitors will be provided with a detailed training manual that they will be required to follow in their home visits. All of the assessment tools they have used during the first three in-home sessions will be reviewed during the second training day and used to formulate a case analysis and intervention goals. Intervention targets and strategies will be reviewed during the third training day.

Due to the design of the study whereby health visitors each have one intervention family and one control family, a contamination procedure will be put in place. To monitor potential contamination, health visitors will be required to keep a record of the frequency of in-home visits including whether they have seen the control family as part of usual care. If high levels of contamination are found, this information will be added to the analysis as a controlling variable. Also, researchers are blind to participant allocation; however, it is possible that participants may reveal their allocation to the researchers at the follow-up data collection visit. Researchers will be asked to record if unmasking has occurred and, again, if high levels of unmasking are found, a variable will be added to the analysis to control for this.

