An experienced clinician (the second author) who developed the EPaS programme will conduct the training. After completing the first day of training, health visitors will begin visiting an intervention family weekly for up to 12 1-hour in-home sessions. The total number of in-home visits may vary between families depending on the complexity of the problem behaviours being targeted. Health visitors are asked to keep a record of the number of visits completed with the intervention family. All intervention resources are provided including a detailed training manual, the assessment tools for the information-gathering sessions, and packs of carbonated paper for drawing up record sheets and writing weekly targets for families. Envelopes and stamps are also given to the health visitors so they can send things to parents such as appointment letters, and so that parents can send completed records to their health visitor for feedback such as record sheets, completed assessments, and so on. Control families receive treatment as usual during this first phase and are offered the treatment 6 months later. During the 6-month wait the control group will receive usual care from the health visitors. Control families can contact their health visitor if any behavioural issues become problematic for them. This can consist of targeting problem behaviours such as sleeping, eating, and toileting using standard behavioural techniques. Control families will complete all outcome measures at the same time as the intervention group, approximately 6 months postbaseline.

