### Statistical analyses

Baseline characteristics of the sample (health visitor, parent, and child) will be analysed and checked for differences (if any) between the two conditions, intervention and waiting-list control and any differences will be recorded.

The main analyses will be performed using the entire intention-to-treat population. The primary outcome measure, the change in the scores on the parent-reported ECBI from baseline to follow-up, will be calculated for each individual and compared between conditions using multiple linear regressions, controlling for any differences in sample characteristics at baseline and the baseline scores on the ECBI. Study site will also be controlled for in the analyses to assess any effects of clustering.

Secondary outcome measures that assess changes from baseline to follow-up in child behaviour, parental practices, and parental depression will also be analysed using multiple linear regressions, controlling for any differences in sample characteristics at baseline, baseline scores of the relevant outcome measure, and study site. In addition to the intention-to-treat analyses, per-protocol analyses will be conducted on data from participants who have remained in the study and have completed measures at all time points.

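### Contamination and unmasking, both arising after randomisation, may be added as covariates with nothing confining this to a sensitivity analysis; in the main model it could bias the effect either way

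*Protocol article*

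**What the plan says.** The Intervention fidelity section of the protocol article sets two conditional rules. For contamination: "If high levels of contamination are found, this information will be added to the analysis as a controlling variable". For researchers who learn the allocation: "if high levels of unmasking are found, a variable will be added to the analysis to control for this".

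The contamination information is a log: "health visitors will be required to keep a record of the frequency of in-home visits including whether they have seen the control family". Unmasking belongs to the end of follow-up: "it is possible that participants may reveal their allocation to the researchers at the follow-up data collection visit".

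The Intervention section describes what such a log would pick up. In the intervention arm, "health visitors will begin visiting an intervention family weekly for up to 12 1-hour in-home sessions". In the control arm, "Control families can contact their health visitor if any behavioural issues become problematic for them", and usual care may then include standard behavioural techniques.

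The Statistical analyses section states: "The main analyses will be performed using the entire intention-to-treat population". It describes the primary regression as "controlling for any differences in sample characteristics at baseline and the baseline scores on the ECBI", and adds study site. It mentions neither contamination nor unmasking.

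**The concern.** A regression on randomised arm keeps its causal reading if the other covariates were fixed before randomisation. Neither of these was.

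- **Visit count.** In the intervention arm, home visits carry the treatment. Holding visits constant removes whatever part of the benefit they deliver. In the control arm, contact is prompted by behaviour problems, so visits also carry prognosis.
- **Control-family-seen flag.** If the flag is zero for every intervention family, the arm coefficient compares intervention families with unseen controls only. Controls who were seen drop out of the contrast.
- **Unmasking flag.** This is recorded when the outcome is measured, and may depend on both arm and outcome. If so, adjusting for it opens a non-causal path. For the primary outcome there is also little to gain: the ECBI is parent-reported, and the Blinding section says that parents know their allocation.

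What is at stake is whether the headline coefficient estimates the effect of offering EPaS. The Sample size section already calls the target of 0.55 SD optimistic and a larger sample hard to recruit, so there is little margin for lost effect or precision.

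**Working it through.** **The plan's own figure.** For 0.55 SD, 80% power and 5% two-sided significance (sidedness assumed), n per arm = 2(1.960 + 0.842)²/0.55² = 51.9, so 52; the t-test version gives 53. The plan states 55, at which power is 0.816. With 10% dropout, 52/0.9 gives 58 and 55/0.9 gives 62; the plan states 60. The sample size is not at issue.

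**Set-up of the check.** 55 per arm, outcome SD about 1, benefit positive, target effect 0.55 SD, 3,000 simulated trials, regression on arm with and without the extra covariate. Outcome includes −0.5u, where u is severity and should be read as the part that baseline ECBI does not capture. Pairing within health visitor is ignored. Every contamination and unmasking input is an assumption.

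The results can be checked by hand from the covariance-adjustment identity:

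adjusted effect = unadjusted effect − γ × (difference between arms in the mean of the covariate),

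where γ is the pooled within-arm slope of outcome on covariate.

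**Visit count as covariate.** Intervention visits have mean 10 and SD 2. Control visits are max(0, 2 + need × u + noise of SD 2), with mean 2.17 if need = 0 and 2.23 if need = 1.

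- *Benefit through visits, no link to need.* γ = 0.55/8 = 0.0688 and the difference is 7.83. Unadjusted 0.0688 × 7.83 = 0.54; adjusted 0.54 − 0.54 = 0. Simulated: 0.54 to −0.01, SE 0.19 to 0.45, power 80% to about 6%.
- *Benefit through visits, control visits rise with need.* Need contributes −0.0538 to γ, so γ = 0.0149. Adjusted = 0.534 − 0.0149 × 7.77 = 0.42. Simulated: 0.53 to 0.40, power 79% to 16%.
- *Benefit not through visits, control visits rise with need.* γ = −0.0538. Adjusted = 0.55 + 0.0538 × 7.77 = 0.97. Simulated: 0.55 to 0.97.

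**Control-family-seen flag.** A fraction p of controls is seen and receives half the effect, so the intention-to-treat effect is 0.55 − p × 0.275: 0.495 at p = 0.2 and 0.44 at p = 0.4. The adjusted coefficient is intervention minus unseen controls: 0.55 − 0.5 × s × φ(q)/(1 − p). Here s is the correlation of being seen with severity, and q is the normal cut-point for p. The ratio φ(q)/(1 − p) is 0.350 at p = 0.2 and 0.644 at p = 0.4.

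| Who is seen | p = 0.2 | p = 0.4 |
|---|---|---|
| Intention to treat, unadjusted | 0.495 | 0.44 |
| Random (s = 0), adjusted | 0.55 | 0.55 |
| Worse families (s = 0.5), adjusted | 0.46 | 0.39 |
| Worse families (s = 0.8), adjusted | 0.41 | 0.29 |
| Better families (s = −0.5), adjusted | 0.64 | 0.71 |

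The simulated means agree to within 0.01.

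**Unmasking flag.** Probability 40% v 10% at outcome zero, with log-odds rising by k per SD of improvement.

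- k = 0: γ = 0, so 0.55 stays 0.55; simulated power falls from 81% to 76%.
- k = 0.5: rates 47% v 11%, γ = 0.477, adjusted 0.55 − 0.477 × 0.36 = 0.38; simulated power 45%.
- k = 1: rates 53% v 13%, γ = 0.847, adjusted 0.55 − 0.847 × 0.396 = 0.21; simulated power 19%.
- With no true effect, the adjusted mean is −0.14 (k = 0.5) or −0.24 (k = 1), and null rejection is 12% or 24% instead of 5%. The shift is towards apparent harm, not false benefit.

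**The case against.** The strongest defence is that the rule may never touch the primary result. It applies only if contamination or unmasking proves high, it speaks of the analysis without calling it primary, and the Statistical analyses section lists only baseline variables and site. A reader might infer that the plan commits to adjusting the primary comparison, or that doing so will remove the effect. The article supports neither. It leaves open which model is meant, and the loss of the whole effect needs two further assumptions: that visit count in both arms is the covariate, and that benefit acts through visits.

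Nor is bias inevitable. Unmasking unrelated to outcome within arm costs only precision. Random contamination gives back 0.55 from a diluted 0.44 to 0.495, which is a different estimand rather than a lost effect. Nothing in the article says that improved families disclose more often.

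The absence of a threshold is not a fault to raise here, since an analysis plan or full protocol could define it.

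All of this stands, and it limits the point. It does not justify the rule as written. Nothing confines the adjustment to a sensitivity analysis, and the Intervention section itself describes control contact driven by need. The plan cannot know beforehand which of the benign or harmful cases will hold.

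**Conclusion.** The concern holds in a conditional form. The Intervention fidelity section allows covariates that arise after randomisation, the Statistical analyses section describes an intention-to-treat model without them, and the two must be reconciled. If the rule reached the main model, the coefficient would no longer estimate the effect of offering EPaS and could be biased either way.

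Under the assumed inputs, the adjusted estimate ranges from about 0 to 0.97 SD against a target of 0.55 SD. Flags related to outcome give about 0.2 to 0.46 if worse-off controls are seen or improved families disclose, and 0.64 to 0.71 if better-off controls are seen. There is no bias, only lost precision, where the flags are unrelated to outcome within arm and control contact carries no EPaS content. These figures show what the rule can do; they do not forecast this trial. The point should be fixed, but because the rule is conditional and absent from the stated primary model, it does not by itself invalidate the plan.

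**What to change.** State in the protocol or analysis plan that the primary and secondary intention-to-treat models contain baseline covariates and study site only, with no variable arising after randomisation. Replace the two adjustment rules with a commitment to report home visits, control-family contact and unmasking by arm. Place any adjustment for contamination or unmasking in a labelled, pre-specified sensitivity analysis, with a note that it targets a different quantity and is open to confounding.

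Optional, and not needed to settle the point: recording which EPaS components were used with control families, an instrumental-variable analysis based on that record, and collecting assessors' guesses of allocation. These need data that the article does not describe collecting, and its Trial status section says that recruitment has begun, so such data could be incomplete.

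The required change costs wording only. The sample size is unchanged, and no extra families or visits are needed.

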### Study outcomes

#### Screen

A parent-reported measure will be administered to determine the eligibility of children for inclusion in the study. The measure is the ECBI, a 36-item inventory completed by the parent for the assessment of frequency and intensity of behavioural problems in children aged 2 to 16 years [35]. Only children who score above the clinical cut-off on either the intensity subscale (≥131) or the problem subscale (≥15) will be eligible to participate. The questionnaire demonstrates good stability and homogeneity, with reliability coefficient of .86 for test-retest and .98 for internal consistency [36]. The ECBI has shown good convergent validity with scores being significantly correlated with scores on the Child Behaviour Check List [37]. Health visitors will be responsible for collecting and scoring this data for screening purposes only. Follow-up ECBI data will be collected by researchers blind to condition allocation.

### Primary outcome

The primary outcome is to establish whether there is a significant change in child behaviour from baseline to follow-up in the parent-reported ECBI.

### Secondary outcomes

The following secondary outcomes will be collected at both time points by the research team:Child hyperactive behaviour measured on the Conners Abbreviated Parent-Teacher Questionnaire [38]. This is a ten-item scale that comprises of the most highly loaded symptoms from the factor scales of the Conners Parent and Conners Teacher Rating Scales. Responses are rated on a 4-point scale ranging from 1 (not at all) to 4 (very much). A clinical cut-off score for hyperactivity is recommended as 15 [38].Observation of parent–child interaction, based on the categories from the Dyadic Parent–child Interaction Coding System (DPICS) [39]. Six parent and four child categories are employed, summarised in terms of parent positive behaviour, parent negative behaviour, child positive behaviour, and child deviance. Observational coding is continuous and records the total frequency of each behaviour per specified interval. For this study, the primary caregiver is observed interacting with their child in their own home for 30 minutes. The DPICS has shown good reliability as evidenced by a number of studies [5, 18]. Inter-rater reliability levels will be assessed during this study (20% of all observations at both time points)Negative parenting practices measured on the Arnold-O’Leary Parenting Scale [40]. This is a 30-item inventory that includes 3 subscales: laxness, over-reactivity, and verbosity. Responses are recorded on a seven-point scale anchored between two alternative responses to a particular situation. The questionnaire has shown adequate internal consistency (α = .63 to .84) and good test-retest reliability (*r* = .79 to .84) [40]Parental depression measured on the Beck Depression Inventory II (BDI) [41]. This is a 21-item inventory designed to assess the severity of characteristic symptoms and attitudes associated with depression. Each item contains 4 possible responses ranging from 0 (for example, I do not feel sad) to 3 (for example, I am so sad or unhappy that I cannot stand it). The clinical cut-off scores for this measure are as follows: minimal (0 to 13), mild (14 to 19), moderate (20 to 28), and severe (29 to63). The BDI has shown high internal consistency (α = .92), good test-retest reliability (*r* = .93), and good convergent validity (*r* = .93) [41]

An additional secondary outcome, parental satisfaction with the intervention, will be collected by the health visitors during their last in-home sessions with the parents. This is to ensure that the research team remains blind to participant group allocation.

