### Recruitment

Health-visiting service managers will be approached and asked if they are interested in their staff participating in the trial. If they are, the managers are asked to identify health visitors within their service who would be interested in participating in the study. A member of the research team will then meet with interested health visitors to discuss the study and provide information regarding the commitment. Health visitors are given an Information Sheet to read and have the opportunity to ask any questions. If they agree to participate, the researcher will obtain informed consent from each health visitor. Once they have consented, they are given a pack of recruitment materials. These include the child behaviour questionnaire (the Eyberg Child Behaviour Inventory, ECBI), instructions on how to administer and score the ECBI, Note of Interest forms for eligible, interested parents to complete, freepost envelopes to send the completed ECBIs and Note of Interest forms to the research team, and a copy of the Information Sheet for parents.

Health visitors are asked to approach families on their caseloads that have a child aged between 30 and 48 months and have expressed concerns about their child’s behaviour. They ask the parents to complete the ECBI questionnaire. If they do not score above the clinical cut-off for child behaviour problems, the health visitor will thank them for their time and proceed to find an eligible family. If they score above the clinical cut-off for one of the two subscales (Intensity or Problem) the health visitor will introduce the project and ask the parent if they would be interested in taking part. If they respond positively, they are asked to complete a Note of Interest form that gives permission to the research team to contact the family to discuss the project further. The health visitor also leaves an Information Sheet for the parent to read before the visit by a researcher and then forwards the Note of Interest and completed ECBI to the research team.

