## Discussion

This trial will provide important information on the effectiveness of an enhanced version of the EPaS programme, a one-to-one intervention to address behaviour problems in young children. The effects of the intervention on child behaviour, parenting behaviour, and parental depression will be assessed. This is a timely project when considering the rising levels of behaviour problems and the government’s focus on the importance of early intervention [1, 48].

One of the challenges of conducting this research will be the recruitment of ‘hard to reach’ families. These families can be difficult to work with due to their lack of engagement with services and/or difficulties accessing services. This is why health visitors will be identifying families for the trial as well as delivering the intervention. Other research with parenting programmes has shown that health visitors are effective in identifying parents in need of support for their child’s behaviour problems, with 81% of families identified agreeing to a visit from a researcher and 93% of those families giving informed consent [18]. Health visitors will identify families from their own caseloads so they should already have a good relationship with the families. The parents may also feel more willing to take part knowing that they will be working with their own health visitor. Health visitors will be fully aware of the details of the study and will be briefed on the best means of presenting the study in a positive way to parents.

This is the first rigorous evaluation of the EPaS 2014 programme and will potentially be a valuable addition to the child behaviour problem literature. It is hypothesised that EPaS 2014 will improve a range of outcomes, including child behaviour, parent behaviour, and parental depression, for families with a young child identified with behavioural problems. If significant results are found, the intervention may be available for use by health visitors on a more regular basis.

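### Parental satisfaction is collected by the health visitor who delivered the programme, and only at the last session: it is at risk of upward bias and omits families who disengage

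*Protocol article*

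**What the plan says.** Under Secondary outcomes, the article lists the hyperactivity, observation, parenting and depression measures with the introduction "The following secondary outcomes will be collected at both time points by the research team". Satisfaction is then set apart: "An additional secondary outcome, parental satisfaction with the intervention", which "will be collected by the health visitors during their last in-home sessions with the parents". One reason is given: "This is to ensure that the research team remains blind to participant group allocation".

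Three other places bear on this:

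- **Intervention:** after the first training day "health visitors will begin visiting an intervention family weekly for up to 12 1-hour in-home sessions". The person who collects the rating is thus the person who delivered the programme. The same section adds: "The total number of in-home visits may vary between families depending on the complexity of the problem behaviours being targeted".
- **Discussion:** "Health visitors will identify families from their own caseloads so they should already have a good relationship with the families".
- **Randomisation and Blinding:** each health visitor has one intervention and one control family. Parents and health visitors know the allocation, and the staff who collect outcome data do not.

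**The concern.** Two features of the stated method could push the result in the same direction.

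1. **Who collects.** The parent gives an opinion of the programme to the professional who delivered it, who was known to the family beforehand and may well go on seeing them. The object of the rating is the intervention, not the health visitor. But the content is individualised and delivered one to one, so the two are hard to separate in a parent's mind. Parents tend to be polite in that position.
2. **When it is collected.** The form is tied to a last session. A family that withdraws without one has no described way to respond, and such families may be less satisfied than those who finish. The Discussion itself describes the target families as hard to engage.

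At stake is how well one descriptive secondary outcome represents all families offered the programme. The estimate of effect is not at stake.

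**Working it through.** **Plan's own figure.** The article gives no satisfaction scale, expected rate or programme-completion rate, so there is nothing to reproduce. The sample-size calculation concerns the ECBI and does not bear on this point.

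**Does the blinding reason require this route?** Blinding requires that those who collect outcome data do not learn who received the programme. Only intervention families can rate it before the 6-month follow-up, so the data collectors should not handle the form. That does not mean the provider must handle the answers. Under Randomisation, the second author carries out the allocation, so at least one team member knows it and cannot be among the blinded data collectors. A recipient who is neither provider nor blinded assessor is therefore available.

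**Who is missed?** Visit numbers vary by design, so a family that finishes early by agreement still has a last session and can be asked. The gap concerns only families that disengage without one.

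**Illustration of the selection effect (assumed rates).** Let *d* be the share of intervention families with no last session, *p*₁ the satisfied share among families who reach one, and *p*₀ the satisfied share among those who do not. The plan reports *p*₁. The value for all families is (1 − *d*)*p*₁ + *d p*₀, so the overstatement is *d*(*p*₁ − *p*₀).

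Assume *p*₁ = 90%. The article's 10% drop-out is loss from the study, not from home visits, and is borrowed here only as a starting value for *d*. It would be 6 of 60 families.

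| *d* | *p*₀ = 0% | *p*₀ = 40% | *p*₀ = 60% |
|---|---|---|---|
| 10% | 81% (9 points) | 85% (5) | 87% (3) |
| 20% | 72% (18) | 80% (10) | 84% (6) |
| 30% | 63% (27) | 75% (15) | 81% (9) |

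Each cell gives the value for all families, with the overstatement in brackets. For example, 0.9 × 0.90 + 0.1 × 0.40 = 0.85. If those who stop are as satisfied as the rest (*p*₀ = 90%), the overstatement is 0.

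**Against sampling error.** With 54 respondents at 90%, the standard error is √(0.9 × 0.1 / 54) = 0.041, so the 95% interval is about ±8 points. A gap of 3 to 5 points is smaller than that.

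**Courtesy bias.** This would be added to the above. The article offers no basis for sizing it.

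**The case against.** The strongest reply is that the article says only that health visitors collect the rating. It does not say that they ask the questions aloud, see the answers or receive an open form. Private completion and sealing are operating details that an article may leave to the full protocol. This stands. A reader might infer that the result is certainly biased upward, or that it cannot reveal dissatisfaction, but the text does not support either. It supports a risk. If a sealed form is already in use, the sponsor need only say so, and the question of families who disengage remains.

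A second reply is that posting forms back could harm blinding. This also stands for a simple version of the change. Only intervention families would return an envelope, so an identifiable one reaching a data collector would reveal that family's allocation and, by the pairing, the control family's too. The recipient and the time of opening must be fixed accordingly. Nor do the envelopes already supplied set a precedent for bypassing the health visitor. Under Recruitment they are for the health visitor's own use ("freepost envelopes to send the completed ECBIs and Note of Interest forms to the research team"), and under Intervention they let parents return records to the health visitor. They show only that postage is already provided for.

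A third reply is that little depends on the measure. It has no control-arm counterpart before follow-up, and it is absent from the secondary outcomes named under Aims and objectives and from those listed for regression. A reader might infer that satisfaction will be used to justify routine use. The Discussion links wider use to significant results and does not mention satisfaction. This limits the importance of the point but does not remove it, because the article itself names satisfaction as an outcome.

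**Conclusion.** The point holds as a risk, not as a demonstrated bias. A named secondary outcome is collected by the provider, only at a last session, for a reason that does not require the provider to handle the answers. The likely direction is upward, on the assumptions that parents soften criticism in front of the provider and that families who disengage are less satisfied. The documents establish neither.

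The size cannot be computed from the article. The figures in the table rest wholly on assumed rates, and at 10% stopping early with 40–60% of them satisfied the gap lies within sampling error. The primary outcome, the sample size and all between-arm comparisons are unaffected. The change is worth making because it is cheap; it is not essential to the trial.

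**What to change.** Amend the paragraph on satisfaction under Secondary outcomes as follows:

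1. At the last session the health visitor hands over the form. The parent completes it privately and seals it, and the health visitor does not see the answers.
2. Intervention families who stop without a last session are posted the same form with a stamped envelope.
3. Envelopes carry a study number only. They are returned to a team member who already knows allocation and collects no outcome data, never to the blinded data collectors. The author who carries out the randomisation also developed the programme and trains the health visitors. If that author is the recipient, someone else could score the forms.
4. Envelopes stay unopened until follow-up is complete for both of that health visitor's families.
5. The report gives the number returned out of all families allocated to the intervention, beside the satisfaction result.

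If the full protocol already provides for a sealed form, item 1 needs only a sentence to say so.

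The cost is about sixty envelopes, some handling and a few lines of procedure. The downside is that some posted forms will not come back. Reporting returns against all allocated families at least makes that loss visible.
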